### Sample size calculations

As this is a pilot study, a formal sample size calculation is not warranted. One of the aims of the study is to generate the estimates needed for a sample size calculation for a future definitive trial. In order to generate the reliable estimates needed, it is proposed that six clusters (three in the intervention arm, three in the control arm) each containing 10 patient participants are recruited. Each cluster will be an independent GP practice, meeting the inclusion criteria laid out in
Table 1. The number of clusters chosen is governed by pragmatism and to provide a representative sample (using best judgement) of the diversity in the population of clusters from which data in the definitive trial will be sampled. 

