### Progression to a full RCT

The following pre-defined stop/go criteria in
Table 4 will be used to inform the decision on whether to proceed to a full trial.

**Table 4. T4:** Stop/go criteria.

	Go – proceed with full RCT	Amend – proceed to full RCT with changes	Stop – do not proceed unless major changes are possible
1. Feasibility of practice recruitment Can 6 practices be recruited to take part in 3 months?	If ≥5 practices are recruited to take part in 3 months	If ≥5 practices are recruited, but it takes longer than predicted (e.g. 3–6 months)	Unable to recruit at least 4 practices.
2. Feasibility of patient recruitment Can 10 patients per practice (total n = 60) be recruited?	If 8–10 patients are recruited in one month per practice: total of 60 (100%)	If 6-7 patients are recruited in one month per practice: total of 36–60 (60% to ≤100%)	If <6 patients are recruited in one month per practice: total of ≤36 (<60%)
3. Feasibility of practice retention Can all 6 practices be retained in the study until completion?	≥5 retained	≥4 retained	≤3 retained
4. Feasibility of patient retention * Can at least 90% of recruited patients be retained in the study until completion?	>9 patients (90%) retained	7–8 patients (70-80%) retained	<7 patients (<70%) retained
5. Intervention feasibility	Delivery of intervention judged strongly feasible by qualitative data	Delivery of intervention judged mainly feasible by qualitative data	Delivery of intervention judged problematic by qualitative data

**Retention will be defined as availability of final outcome measures*.

The Decision-making after Pilot and feasibility Trials (ADePT) process involves examining 14 methodological issues that are pertinent to feasibility research. We will use this process, as well as the progression criteria, findings from the qualitative research, and discussions with the study research team, Trial Management Group, Trial Steering Committee and the public and patient involvement (PPI) panel to make a decision on whether to progress to full RCT.

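### Table 4's patient-retention rule gives no verdict at its own 90% target: Go requires more than 9 of 10, and Amend ends at 8

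*Protocol article*

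**What the plan says.** The section on progression to a full RCT lists five stop/go criteria in Table 4. Criterion 4 asks: "Can at least 90% of recruited patients be retained in the study until completion". Its three cells are:

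- Go: ">9 patients (90%) retained"
- Amend: "7–8 patients (70-80%) retained"
- Stop: "<7 patients (<70%) retained"

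A footnote adds: "Retention will be defined as availability of final outcome measures".

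The denominators come from elsewhere. The sample size section plans "six clusters (three in the intervention arm, three in the control arm) each containing 10 patient participants are recruited", and criterion 2 asks "Can 10 patients per practice (total n = 60) be recruited". Criterion 3, on practices, asks "Can all 6 practices be retained in the study until completion" and gives Go if five or more are retained, Amend if at least four, and Stop if three or fewer.

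The same section says that the decision will also draw on the ADePT process, the qualitative findings and discussion with the trial's committees and the PPI panel.

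**The concern.** A pre-defined progression criterion should give every possible result a verdict before the data are seen. This row does not. Its question sets the target at 90% or above, its Go cell carries a 90% label, and yet the count in that cell excludes 90%. A practice that exactly meets the target is neither Go nor Amend.

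The row also leaves its unit open. The question is about recruited patients as a whole, while the cells count out of 10. If the percentages are applied to the whole trial, the interval between 80% and 90% has no verdict.

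At stake is whether the retention verdict is fixed in advance. Retention is part of the trial's second objective, and results near the target are the ones a successful pilot would produce. If the result lands in the gap, the team must choose the label after seeing it.

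**Working it through.** **Inputs.** 10 patients per practice, six practices, 60 in total (sample size section; Table 4, criterion 2). Bands as printed in criterion 4. The document gives no expected retention rate, so the rates of 80% to 95% below are assumptions. Independence between patients is also assumed.

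**Step 1: the printed Go threshold.** The cell equates more than 9 patients with 90%. Of 10 patients, 9/10 = 90% and the only count above 9 is 10/10 = 100%. The label is not reproduced.

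**Step 2: every result for one practice of 10.**

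| Retained | Verdict as printed | Verdict if Go is 9 or more |
|---|---|---|
| 0–6 | Stop | Stop |
| 7–8 | Amend | Amend |
| 9 | none | Go |
| 10 | Go | Go |

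**Step 3: the same percentages on the pooled total.** For 60 patients, 70% = 42, 80% = 48 and 90% = 54.

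- Literal reading (Go above 90%): Stop 0–41, Amend 42–48, none 49–54, Go 55–60.
- Corrected reading (Go at 90% or more): Stop 0–41, Amend 42–48, none 49–53 (49/60 = 81.7% to 53/60 = 88.3%), Go 54–60.

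If 50 patients are recruited, the gap is 41–45 on the literal reading and 41–44 on the corrected one.

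**Step 4: how likely the gap is.** With X binomial(n, p), P(X = k) = C(n, k) p^k (1 − p)^(n − k). For one practice at p = 0.90, P(9 of 10) = 10 × 0.9^9 × 0.1 = 0.387 and P(10 of 10) = 0.9^10 = 0.349. Pooled probabilities sum the same formula with n = 60.

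| True retention | Exactly 9 of 10 | 10 of 10 | 49–53 of 60 | 49–54 of 60 |
|---|---|---|---|---|
| 0.80 | 0.268 | 0.107 | 0.418 | 0.437 |
| 0.85 | 0.347 | 0.197 | 0.635 | 0.723 |
| 0.90 | 0.387 | 0.349 | 0.379 | 0.548 |
| 0.95 | 0.315 | 0.599 | 0.030 | 0.079 |

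At a true rate equal to the target, a single practice is slightly more likely to get no verdict (0.387) than Go (0.349).

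**Step 5: reading criteria 3 and 4 together.** Suppose six practices of 10 are recruited, one is lost, and its patients have no final measures. Criterion 3 gives Go (5 retained). Patient retention is at most 50/60 = 83.3%, which cannot be Go and lies in the pooled gap. If only five practices are recruited and all five stay, up to 50/50 = 100% is possible and the two criteria agree.

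**The case against.** The strongest reply is that this is a one-character slip with its correction in the same row: both the question and the percentage label point to 9 or more. That is probably right, and with it the per-practice bands are complete. What remains is that the printed rule says otherwise, and that correcting the sign does not settle the unit.

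A second reply is that the cells count out of 10 and that 70–80% merely restates 7–8 of 10, so the pooled gap comes from a reading the cells do not state. This has force. But the question concerns all recruited patients, and criterion 2 gives both a per-practice count and a total where criterion 4 does not. The unit is open, and under one of the two readings the gap survives.

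Third, the criteria only inform a decision that also uses other evidence. This stands and limits the severity.

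Three stronger readings are tempting but not supported:

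- A reader might infer that Go needs every practice to pass separately, making it almost unattainable. Table 4 never says so.
- A reader might infer that criteria 3 and 4 contradict each other. They are separate domains and may differ. The mismatch needs six practices recruited, one lost, and no final measures for its patients. The Study status section reports five practices so far, and follow-up questionnaires are given at the practice, but chart-review outcomes might still be available.
- A reader might infer that the footnote lets chart-review data alone count as retention, so that Stop could hardly occur. The footnote speaks of final outcome measures in the plural without saying which, and an article may leave that detail to the full protocol.

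**Conclusion.** The point holds, at moderate severity. As printed, criterion 4 gives no verdict at exactly 9 of 10, which is its own target; this follows from the text and needs no assumption. Reading Go as 9 or more removes that gap for a single practice. If the rule is applied to all 60 patients, 49–53 retained still has no verdict, or 49–54 if the sign is taken literally. The two pooled ranges belong to different readings of the sign and should not be mixed.

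The probabilities at true retention of 90% (0.39 for 9 of 10; 0.38 or 0.55 pooled) are illustrative. They assume independent patients, whereas patients within a practice may drop out together, and the true rate is unknown. Across assumed rates of 80% to 90% the pooled gap is substantial under either reading; at 95% it is small (0.03 or 0.08).

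The mismatch with criterion 3 is secondary and conditional. None of this invalidates the progression decision, since no cell of Table 4 triggers it automatically.

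**What to change.** State that criterion 4 is judged on all recruited patients, and replace its cells with contiguous bands that keep the protocol's own 90% and 70% cut-points, scaled to the number actually recruited:

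| Verdict | Share retained | Of 60 | Of 50 |
|---|---|---|---|
| Go | 90% or more | 54–60 | 45–50 |
| Amend | 70% to below 90% | 42–53 | 35–44 |
| Stop | below 70% | 0–41 | 0–34 |

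Report retention both over all recruited patients and within retained practices, so that the loss of a whole practice can be told apart from individual dropout when criteria 3 and 4 are read together.

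The cost is the wording of one table row and one extra line in the report, with no new data. The change should be made before follow-up retention is known.

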### Study within a trial (SWAT)

A pilot SWAT (study within a trial) will be embedded within this pilot RCT. The objective of the SWAT will be to evaluate the effect of a video outlining the importance of the research on retention to the study. This is in line with objective 2 of the pilot RCT, and will provide additional data on the feasibility of retention to the study. Videos have been used in the past to improve recruitment to studies
^
39,
40
^ and it is possible that this effect may also apply to retention. Half of the patient participants will be randomised to the intervention group. Randomisation will be at the individual, rather than cluster level, meaning participants in all clusters will have an equal chance of receiving the intervention, regardless of pilot RCT arm allocation. Those in the SWAT intervention group will receive a text message with a link to the video at the mid-point of the study. The control group will not receive a text message and progress through the study as usual. The video will be less than five minutes long and contain information on the prevalence of high blood pressure, risks of high blood pressure, and justification for the current research. The primary outcome will be the number and proportion of participants who are retained in the study; however, as this is a pilot SWAT, we will not test for effectiveness. We will analyse the feasibility and acceptability of the SWAT through descriptive statistics, including the an adaptation of the Decision Making Questionnaire
^
41
^ and qualitative work.

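### Retention criterion 4 pools all recruited patients, half of whom are randomised to a video meant to improve retention, so the figure may describe neither way of running the definitive trial

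*Protocol article*

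**What the plan says.** The Protocol article, under Study within a trial (SWAT), embeds a second randomisation in the pilot: "Half of the patient participants will be randomised to the intervention group. Randomisation will be at the individual, rather than cluster level". Patients in every practice and in both MIAMI arms can be allocated. Those allocated receive a text link to a short video halfway through; the others receive nothing. The SWAT's purpose is to evaluate the video's effect on retention. Its primary outcome is how many patients, and what share, stay in. No effectiveness test is planned. An effect on retention is put forward only as a possibility, by analogy with recruitment videos, and no size is given.

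Under Progression to a full RCT, Table 4 makes retention one of five pre-defined criteria. Criterion 4 asks "Can at least 90% of recruited patients be retained in the study until completion". Its Go cell reads ">9 patients (90%) retained" and its Amend cell "7–8 patients (70-80%) retained"; fewer than 70% is Stop. A footnote defines retention as having the final outcome measures. Neither the table nor the text around it says how SWAT groups are handled in this criterion. The planned size is "six clusters (three in the intervention arm, three in the control arm) each containing 10 patient participants are recruited".

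**The concern.** One outcome does two jobs. Retention is the endpoint of an embedded experiment that tries to raise it in half the sample. It is also a criterion for deciding whether the definitive trial is feasible. Video recipients are recruited patients, so criterion 4 counts them, whether its counts are applied per practice or across the study.

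If the video works, the observed retention is a half-and-half mixture. A definitive trial will presumably either use the video for everyone or not use it, and the pooled pilot figure estimates neither. Where retention without the video is a little under 90%, the mixture can turn a probable miss of the Go threshold into a probable pass. If nothing is settled beforehand, the choice between the pooled and the split figure could be made after the data are seen.

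**Working it through.** **Inputs from the Protocol article.** Six practices of 10 patients (Sample size calculations); total 60 (Table 4, criterion 2); half allocated to the video, so about 30 and 30 (SWAT section); 90% retention target (Table 4, criterion 4).

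**Assumptions, because the article gives no figure.** Retention without the video, p0: 80% to 90%. Video effect, d: 0, 5 or 10 percentage points. Patients are independent; no intracluster correlation is given.

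**Step 1: the plan's own figures.** 6 × 10 = 60 reproduces the stated total. 90% of 60 is 54, or 9 of 10 in a practice. The Go count is written as more than 9 beside 90%. Taken literally, more than 9 of 10 is 10 of 10, or 100%. I use the 90% in the criterion's question, so the threshold is at least 54 of 60.

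**Step 2: shift in the pooled figure.**

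Expected pooled retention = (30 × p0 + 30 × (p0 + d)) / 60 = p0 + d/2.

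The shift is 0, +2.5 and +5 points for d = 0, 5 and 10. Pooled retention therefore overstates retention without the video by d/2 and understates retention with universal video use by d/2. An expected pooled figure of exactly 90% corresponds to p0 = 87.5% when d = 5 and to p0 = 85% when d = 10.

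**Step 3: chance of meeting the threshold.** Retained = X + Y, with X ~ Binomial(30, p0) and Y ~ Binomial(30, p0 + d). P(X + Y ≥ 54) by exact convolution:

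| p0 | d = 0 | d = 5 | d = 10 |
|---|---|---|---|
| 80% | 0.03 | 0.08 | 0.18 |
| 85% | 0.19 | 0.36 | 0.61 |
| 88% | 0.41 | 0.66 | 0.88 |
| 90% | 0.61 | 0.84 | 0.97 |

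**Step 4: sensitivity to the reading of the Go cell.** At p0 = 85%:

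- More than 54 of 60: 0.10, 0.22 and 0.44 for d = 0, 5 and 10.
- At least 9 of 10 in a single practice with a 5:5 video split: 0.54, 0.64 and 0.74.

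The direction is the same on each reading.

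**Step 5: which decision is at stake.** 70% of 60 is 42. At p0 = 85%, P(X + Y ≥ 42) is 0.999 or more for every d considered. Stop is not in play there; the question is whether the pilot reads as Go or as something less.

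**Step 6: precision of a split.** SE = √(p(1 − p)/n). At p = 85%:

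- n = 60: √(0.85 × 0.15/60) = 4.6 points.
- n = 30: √(0.85 × 0.15/30) = 6.5 points.

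Applying 90% to the no-video group alone (at least 27 of 30) gives 0.12, 0.32 and 0.65 at p0 = 80%, 85% and 90%, whatever the video does. At p0 = 85% that 0.32 exceeds the 0.19 for all 60 patients with d = 0, because 30 patients give a noisier count. The split removes the shift but cannot carry the decision alone.

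**The case against.** The strongest reply has three parts. First, the benefit is unproven: the article calls it possible and no more, and with d = 0 nothing is distorted. Second, Table 4 only informs the decision, together with the ADePT process, the qualitative findings and discussion with the committees and the PPI panel, so no automatic rule is corrupted. Third, retention by video group is the SWAT's own primary outcome, so decision makers should have it in hand, and Amend still leads to a full trial with changes. All of this stands, and it limits the seriousness. It does not connect the group-specific figures to criterion 4, which is the one place where a retention threshold was fixed in advance.

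Four stronger readings are tempting and are not supported:

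- *The pilot will pass on retention that the definitive trial would lack.* This assumes that the video works and is then dropped. The article says neither. If a working video were given to everyone later, the pooled figure would be too low.
- *The SWAT allocation is unbalanced across practices or arms.* The article states individual randomisation with equal chances in all clusters. It neither states nor excludes stratification, a detail that a condensed article may leave to the full protocol. It would also matter little: a 17:13 split between arms with d = 10 moves the arm difference in retention by (17 − 13)/30 × 10 = 1.3 points, or 0.4 of a patient in 30. The d/2 shift arises under perfect balance.
- *The video biases the MIAMI comparison.* It will "contain information on the prevalence of high blood pressure, risks of high blood pressure, and justification for the current research", which touches topics that MIAMI also covers. But both arms have the same chance of receiving it, so there is no systematic difference between arms, and the statistical section plans only summary statistics.
- *The video's content must therefore be changed.* That is a design trade-off for the team, and no error in the plan requires it.

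**Conclusion.** The concern holds in a limited form. Criterion 4 is read on all recruited patients, half of whom are randomised to something intended to raise the quantity being judged, and Table 4 does not say how the SWAT groups enter. Pooled retention is shifted by half the video effect. At 85% retention without the video, an effect of 5 to 10 points lifts the chance of reaching 54 of 60 from 0.19 to between 0.36 and 0.61. These figures rest on assumed values of p0 and d and on independent patients; the documents supply none of these. The consequence is mainly a Go that might have been an Amend. It is worth correcting because the change is simple and concerns a threshold fixed in advance, but it does not invalidate the pilot.

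**What to change.** In Table 4, evaluate criterion 4 overall and, beside it, separately for the SWAT video and no-video groups. Give the group results as percentages, since counts out of 10 do not suit groups of about five per practice. State before the data are seen that the group matching the planned use of the video in the definitive trial is read alongside the overall figure when choosing between Go and Amend: the no-video group if the video will not be used, the video group if it will. While editing the row, reconcile the Go count with its own percentage, because 9 of 10 currently falls in neither the Go nor the Amend count.

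The cost is a few lines of text and two extra figures in the retention table, with no new data. The drawback is precision: each group has about 30 patients, with a standard error near 6.5 points at 85% against 4.6 for all 60. The split should qualify the overall result and not replace it.

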### Public and patient involvement (PPI)

The study team includes a public and patient involvement (PPI) panel of six people living with hypertension. This panel meets quarterly and contributes to tasks such as development of the protocol, patient materials and SWAT materials. Two members of the panel also attend and contribute to Trial Steering Committee meetings.

## Ethics and dissemination

Ethical approval has been obtained for all intervention sites from the Irish College of General Practitioners on 23/8/22 (ICGP_REC_22_014). The results of this pilot cluster RCT will be published in a peer-reviewed journal.

## Study status

Five GPs practices have been recruited. Patient participant recruitment began in November 2022.

## Discussion

Supporting GPs and people living with hypertension to work together to maximise medication use has the potential to significantly lower blood pressure in primary care in Ireland. This pilot cluster RCT of the MIAMI intervention will allow us to gather valuable acceptability and feasibility data to further refine the intervention so it optimally designed for both GP and patient use. In particular, the qualitative component will provide an insight into GP and patient experiences of using the intervention.

The pilot cluster RCT will also allow us to the assess the potential feasibility issues involved in running a definitive RCT in the Irish primary care context. One possible difficulty that may arise are the logistics and safety of running such a study during flu season and the possibility of another wave of coronavirus disease 2019 (COVID-19) infection. As this pilot cluster RCT is due to begin in winter 2022, it should allow us to gain an insight into this context.

## Data Availability

No underlying data are associated with this article. Open Science Framework: MIAMI.
https://doi.org/10.17605/OSF.IO/TYAR4
^
23
^. This project contains the following extended data: Consent - GP.doc Consent - patient v2.docx Interview guides.docx Invite letter - GP v2.docx PIL - GP.doc PIL - patient.doc Questionnaire - GP.docx Questionnaire - patient.docx Data are available under the terms of the
Creative Commons Zero "No rights reserved" data waiver (CC0 1.0 Public domain dedication).
